# Individualized positive end-expiratory pressure guided by end-expiratory lung volume in early acute respiratory distress syndrome: study protocol for the multicenter, randomized IPERPEEP trial

**DOI:** 10.1186/s13063-021-05993-0

**Published:** 2022-01-20

**Keywords:** Acute respiratory distress syndrome, Positive end-expiratory pressure, Mechanical ventilation, Ventilator-induced lung injury

## Abstract

**Background:**

In acute respiratory distress syndrome (ARDS), response to positive end-expiratory pressure (PEEP) is variable according to different degrees of lung recruitability. The search for a tool to individualize PEEP based on patients’ individual response is warranted.

End-expiratory lung volume (EELV) assessment by nitrogen washing-washout aids bedside estimation of PEEP-induced alveolar recruitment and may therefore help titrate PEEP on patient’s individual recruitability.

We designed a randomized trial to test whether an individualized PEEP setting protocol driven by EELV measurement may improve a composite clinical outcome in patients with moderate-to-severe ARDS (IPERPEEP trial).

**Methods:**

IPERPEEP is an open-label, multicenter, randomized trial that will be conducted in 10 intensive care units in Italy and will enroll 132 ARDS patients showing PaO_2_/FiO_2_ ratio ≤ 150 mmHg within 24 h from endotracheal intubation while on mechanical ventilation with PEEP 5 cmH_2_O.

To standardize lung volumes at study initiation, all patients will undergo mechanical ventilation with tidal volume of 6 ml/kg of predicted body weight and PEEP set to obtain a plateau pressure within 28 and 30 cmH_2_O for 30 min (EXPRESS PEEP).

Afterwards, a 5-step decremental PEEP trial will be conducted (EXPRESS PEEP to PEEP 5 cmH_2_O), and EELV will be measured at each step. Recruitment-to-inflation ratio will be calculated for each PEEP range from EELV difference. Patients will be then randomized to receive mechanical ventilation with PEEP set according to the optimal recruitment observed in the PEEP trial (IPERPEEP arm) trial or to achieve a plateau pressure of 28–30 cmH_2_O (control arm, EXPRESS strategy). In both groups, tidal volume size, use of prone positioning and neuromuscular blocking agents, and weaning from PEEP and from mechanical ventilation will be standardized.

The primary endpoint of the study is a composite clinical outcome incorporating in-ICU mortality, 60-day ventilator-free days, and serum interleukin-6 concentration over the course of the initial 72 h of treatment.

**Discussion:**

The IPERPEEP study is a randomized trial powered to elucidate whether an individualized PEEP setting protocol based on bedside assessment of lung recruitability can improve a composite clinical outcome during moderate-to-severe ARDS.

**Trial registration:**

ClinicalTrials.govNCT04012073. Registered 9 July 2019.

**Supplementary Information:**

The online version contains supplementary material available at 10.1186/s13063-021-05993-0.

## Background

Mechanical ventilation is the cornerstone treatment of the acute respiratory distress syndrome (ARDS). However, mechanical ventilation can itself initiate and worsen lung damage due to the so-called ventilator-induced lung injury (VILI), which is an inflammatory response that worsens lung function and contributes to the development of the organ dysfunction observed in ARDS patients [1]. Different strategies have been suggested to attenuate VILI: limiting tidal volume (*V*_T_); plateau and driving pressure mitigates lung injury and improves clinical outcome [2–6].

Low *V*_T_ may generate alveolar derecruitment and worsen oxygenation that can be reversed by the application of a positive end-expiratory pressure (PEEP) [7, 8]. It is widely accepted that PEEP setting should aim to a balance between alveolar recruitment (i.e., re-opening of collapsed alveolar units with increased lung volume available for tidal ventilation) and the damage unavoidably generated in the already open tissue. Hence, over the last decade, great effort has been made to identify the PEEP-setting strategy that balances the need for lung recruitment and PEEP-induced alveolar overdistension; PEEP titration methods based on respiratory system compliance [9–11], oxygenation, shunt value s[12, 13], and pressure-volume curve [14] have been proposed. Four different randomized studies comparing higher versus lower PEEP, with high PEEP set according to respiratory system mechanic s[10], oxygenation impairment [12, 13] or to maximize respiratory system complianc e[15], failed to detect a benefit. Higher PEEP however yielded a shorter time to successful weaning in the EXPRESS study, especially in most severe patients [10].

Despite a meta-analysis highlighted a survival benefit in more severe patients treated with higher PEE P[16], the most relevant drawback of such “universal” strategies is that lung recruitability has great inter-individual variability, with high PEEP enhancing lung injury in patients with low recruitability and low PEEP not fully exerting its beneficial effects in recruitable patients [14, 17–20]. Thus, a search for a tool to individualize PEEP on patient’s individual response appears warranted. In spite of encouraging results coming from a preliminary study [21], neither transpulmonary pressure-guided nor driving pressure-driven PEEP did provide benefits in larger trials [15, 22].

Measurement of end-expiratory lung volume (EELV) by the nitrogen washing-washout technique, bedside available from recent ICU ventilators, has been shown to reliably estimate lung aeration and may help mechanistically titrate PEEP on patient’s individual response [23–25].

We designed an open-label, multicenter, randomized trial to test the safety and feasibility of an individualized PEEP setting protocol driven by EELV and to determine whether this may improve a composite clinical outcome in patients with moderate-to-severe ARDS.

## Methods

### Study design

IPERPEEP is an investigator-initiated, multicenter, parallel-group, open-label, two-arm, randomized trial that will be conducted on patients with ARDS and PaO_2_/FiO_2_ ratio equal to or lower than 150 mmHg. The study will be conducted in 10 intensive care units (ICU) in Italy (please refer to Additional file 1 for the details of involved sites). The first patient will be randomized in late 2020. This protocol conforms to the Consolidated Standards of Reporting Trials (CONSORT) guidelines. Figure 1 shows the Standard Protocol Items: Recommendation for Interventional Trials (SPIRIT) schedule of enrollment, interventions, and assessments. By the time of this submission, the protocol has been approved by the ethics committee of the coordinating center (Fondazione Policlinico A. Gemelli IRCCS, ID 38554/18 and 45307/19).

**Fig. 1 Fig1:**
[figure not shown]
Standard Protocol Items: Recommendation for Interventional Trials (SPIRIT) schedule of enrollment, interventions, and assessments. SOFA, Sequential Organ Failure Assessment; CPIS, clinical pulmonary index score; RASS, Ramsay Agitation Sedation Scale; ICU, intensive care unit

There was no public nor patients’ involvement in the design of the trial.

The study has been registered on clinicaltrials.gov (NCT04012073) on July 9, 2019.

### Objectives of the study

The primary objective of the study is to determine whether a PEEP setting protocol driven by EELV measurement may improve a composite clinical outcome in patients with moderate to severe ARDS, as compared to the EXPRESS protocol [10].

### Selection of the participants

All adult ICU patients requiring invasive mechanical ventilation due to acute hypoxemic respiratory failure will be screened for the enrolment. Patients with ARDS and moderate-to-severe oxygenation impairment (PaO_2_/FiO_2_ ≤ 150 mmHg while receiving controlled mechanical ventilation with PEEP = 5 cmH2O) will be the studied population.

Eligibility inclusion criteria for moderate-to-severe ARDS, according to the Berlin definition, will be assessed within the first 24 h from the initiation of invasive mechanical ventilation [26]:
Acute respiratory failure within 1 week of a known clinical insult or new or worsening respiratory symptoms;Bilateral infiltrates at the chest x-ray or CT scan, not fully explained by effusions, lobar/lung collapse, or nodules;Respiratory failure not fully explained by cardiac failure or fluid overload; objective assessment required to exclude hydrostatic edema if no risk factor present.PaO_2_/FiO_2_ ratio ≤ 20 0[27].Written informed consent.

Exclusion criteria will be as follows: pregnancy, pneumothorax, acute brain injury, decompensated heart failure (NYHA 3–4 before the acute phase of the disease or documented ejection fraction< 35% or pulmonary capillary wedge pressure > 18 mmHg) or acute coronary syndrome, intubation as a result of an acute exacerbation of chronic pulmonary disease, body mass index greater than 35 kg/m^2^ or lower than < 35 kg/m^2^, any chronic disease requiring long-term oxygen therapy or mechanical ventilation at home, neuromuscular diseases, severe chronic liver disease (Child-Pugh C or worse), bone marrow transplantation or chemotherapy-induced neutropenia, history of liver or lung transplant, decision to withhold life-sustaining treatment, need for therapy with inhaled nitric oxide due to documented pulmonary arterial hypertension, life-threatening hypoxemia deemed to require extracorporeal membrane oxygenation (ECMO), documented barotrauma, high risk of mortality within 3 months from other than ARDS (severe neurological damage, age > 85 years and cancer patients in terminal stage of the disease), and persistent hemodynamic instability/intractable shock (norepinephrine > 1 mcg/kg/h and/or blood lactate > 5 mmol/L and/or considered too hemodynamically unstable for enrolment in the study by the attending physician).

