### Trial status

Protocol version 2.0, July 2019.

At the time of submission, the regulatory authorization has been obtained in the coordinating center. Enrolment has not yet started in the participating centers. First inclusion is planned in November 2022, and completion of recruitment is estimated to be completed in December 2024.

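### The shock exclusion is set at norepinephrine above 1 mcg/kg/h (0.017 mcg/kg/min), too low for its label yet sufficient alone to exclude: probably a unit error

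*Protocol article*

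**What the plan says.** The last exclusion in the protocol article, Selection of the participants, is "persistent hemodynamic instability/intractable shock (norepinephrine > 1 mcg/kg/h and/or blood lactate > 5 mmol/L", followed by a third alternative: "and/or considered too hemodynamically unstable for enrolment in the study by the attending physician". The label is therefore defined by three limbs: a norepinephrine dose per kilogram per hour, a lactate concentration, and a clinical judgement. Each is linked to the next by and/or, so any one of them suffices.

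Nothing else in the article restates the norepinephrine limit, gives it in another unit, or qualifies it. The same list of exclusions also contains "body mass index greater than 35 kg/m^2^ or lower than < 35 kg/m^2", which cannot be right as printed, since it would leave only patients at exactly 35.

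On where and when the rule applies, the Study design section states: "The study will be conducted in 10 intensive care units (ICU) in Italy". The Trial status section states: "Enrolment has not yet started in the participating centers".

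**The concern.** The label and the number do not match. The label, "persistent hemodynamic instability/intractable shock", describes patients whose circulation cannot be stabilised. The number attached to it is a dose that, once converted to the usual per-minute unit, is very small. It sits next to "blood lactate > 5 mmol/L", which marks serious hypoperfusion. Two alternative markers of the same state should be of roughly similar severity, and these are not.

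Because the limbs are alternatives, the mismatch has effect. A patient with normal lactate, judged stable by the physician, is still excluded if norepinephrine runs above the printed limit. Unlike the body mass index slip, the printed dose can be applied, so a site could follow it without noticing anything wrong.

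What is at stake is who enters the trial. Sites that follow the figure would exclude almost anyone already on norepinephrine. Sites that follow the label would admit patients on far higher doses, each of them a protocol deviation under the printed text. With ten units, the case mix could differ by site for a reason unrelated to the disease. There is also a safety side: after inclusion, PEEP is raised until plateau pressure reaches 28–30 cmH2O (Procedures), so the haemodynamic limit for entry ought to be unambiguous.

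**Working it through.** **Inputs.** From Selection of the participants: norepinephrine limit 1 mcg/kg/h; lactate limit 5 mmol/L; limbs joined by and/or. Body weights of 50, 70 and 100 kg are assumptions, used only to express the limit as an infusion rate.

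**Step 1, conversion to the per-minute unit.** 1 mcg/kg/h ÷ 60 min/h = 0.0167 mcg/kg/min.

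**Step 2, infusion rates under each reading.** As printed, mcg/min = weight × 1/60 and mg/h = weight × 1/1000. If per minute was meant, mcg/min = weight × 1 and mg/h = weight × 60/1000.

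| Assumed weight | As printed (per hour) | If per minute was meant |
|---|---|---|
| 50 kg | 0.83 mcg/min (0.05 mg/h) | 50 mcg/min (3.0 mg/h) |
| 70 kg | 1.17 mcg/min (0.07 mg/h) | 70 mcg/min (4.2 mg/h) |
| 100 kg | 1.67 mcg/min (0.10 mg/h) | 100 mcg/min (6.0 mg/h) |

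The two readings differ by a factor of 60 at any weight.

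**Step 3, other possible intended limits.** The article does not say what was intended, so a range is assumed. The printed limit is too low by these factors:

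| Assumed intended limit | In mcg/kg/h | Factor against the printed 1 mcg/kg/h |
|---|---|---|
| 0.1 mcg/kg/min | 6 | 6 |
| 0.25 mcg/kg/min | 15 | 15 |
| 0.5 mcg/kg/min | 30 | 30 |
| 1 mcg/kg/min | 60 | 60 |

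Even a modest infusion of 0.05 mcg/kg/min is 0.05 × 60 = 3 mcg/kg/h, three times the printed exclusion limit.

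**Step 4, logic of the criterion.** With and/or, the patient is excluded if dose > limit, OR lactate > 5, OR the physician objects. Take a patient on 0.05 mcg/kg/min with normal lactate and no objection from the physician. The second and third limbs are false and the first is true, so the patient is excluded under a heading of intractable shock.

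**Step 5, what is not affected.** The Statistics section asks for 56 per arm with 15% attrition: 56/0.85 = 65.9, so 66 per arm and 132 in total, as stated. The exclusion does not enter this calculation. It is applied before randomization and identically to both arms, so it creates no between-arm imbalance.

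The share of screened patients wrongly excluded cannot be calculated: the article gives no distribution of norepinephrine doses.

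**The case against.** The strongest reply is that calling the dose trace rests on general clinical knowledge, because the article contains no dosing scale, and that 1 mcg/kg/h is a usable threshold. A deliberately strict limit is conceivable before a manoeuvre that raises plateau pressure to 28–30 cmH2O. This does not rescue the text. If a strict limit was intended, the label is wrong and the lactate limb is out of step with it. A correction is needed either way.

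Second, the intended value is unknown, and a wrong number is as possible as a wrong unit. That stands. The per-minute reading is an inference, and the sponsor has to confirm it.

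Third, the article condenses a full protocol (version 2.0, July 2019), and sites also work from a web-based case report form, neither of which is shown. The slip may exist only in the article. This lessens certainty about what sites will apply, but the printed figure is a stated value, not an omission.

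Fourth, the consequences for recruitment and site mix are not quantified, and experienced intensivists may query the figure before acting on it. That is fair and limits the weight of the point, as does the absence of any effect on type I error, power or the treatment comparison.

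Fifth, the timing is not entirely clear. Trial status says enrolment has not begun and plans first inclusion for November 2022, while Study design puts the first randomization in late 2020. The claim that no enrolled patient is affected depends on Trial status being the correct one.

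Two supporting arguments are weak. The body mass index slip shows careless proofreading of the list but does not prove this unit wrong. The secondary endpoint on catecholamine requirements does not show that patients on norepinephrine were meant to be eligible at entry, because vasopressors may be started later.

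**Conclusion.** The concern holds. The printed limit of 1 mcg/kg/h equals 0.0167 mcg/kg/min. It excludes on its own, and it contradicts both the label it defines and the lactate limb beside it. Against an intended limit assumed to lie between 0.1 and 1 mcg/kg/min, it is 6 to 60 times too low. An error of per hour for per minute is the most probable cause, but the article does not establish it.

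The effect is on eligibility, screening yield, consistency across sites and generalisability, and none of these can be sized from the article. There is no effect on the sample size or on the validity of the between-arm comparison. The conclusion rests on the literal text, on simple conversion, and on the clinical premise that such a dose does not mark intractable shock. It merits correction because it is an operative entry rule, though it does not threaten the primary analysis.

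**What to change.** Have the sponsor confirm the intended norepinephrine limit. If per minute was meant, change the unit to mcg/kg/min. If not, either give a dose in mcg/kg/min that matches the shock label, or keep a deliberately low limit and rename and justify the criterion. Use the identical figure and unit in the full protocol, the electronic case report form and the screening log, and inform all ten sites. The body mass index criterion in the same list should be corrected in the same revision.

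The cost is low: one check and a correction to a single threshold, with no change to design, sample size or analysis. If enrolment has not started, as Trial status says, no enrolled patient is touched. If screening has begun at any site, use the screening log to identify patients turned away on the norepinephrine limb alone, and report how many there were.

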### Oxygenation criterion validation

Each patient meeting inclusion criteria will be evaluated for the presence of the oxygenation criterion. After neuromuscular paralysis and endotracheal suctioning, eligible patients will be ventilated for 30 min with PEEP = 5 cmH_2_O in the semi-recumbent position; afterward, arterial blood gas analysis (ABG) will be performed to compute PaO_2_/FiO_2_ ratio. Patients showing PaO_2_/FiO_2_ ≤ 150 mmHg will be enrolled. Patients showing PaO_2_/FiO_2_ < 200 and > 150 mmHg will be treated according to the standard clinical practice and reassessed for the presence of oxygenation criterion within 24 h from endotracheal intubation. To limit the exposure to low PEEP of possibly recruitable patients with severe oxygenation impairment, the ABG certifying the oxygenation criterion will be permitted at any time during the 30-min monitoring period.

### Procedures

After inclusion in the study, all patients will receive continuous neuro-muscular blocking agents (NMBA) infusion for 48 h and will be connected to a mechanical ventilator equipped with EELV measurement module (Carescape R860, GE Healthcare, USA). A standard bi-tube low-resistance circuit with a low-dead space, low-resistance, and high-efficiency heat and moisture exchanger or a heated and humidified bi-tube circuit will be used to connect the patient to the ventilator, according to the preference of the attending physician and the practice of each institution. The use of heated and humidified bi-tube circuits (advised settings: humidification chamber temperature set at 37 °C, absolute humidity provided 44 mgH_2_O/L) will be encouraged in patients that remain hypercapnic (pH < 7.30 and PaCO_2_ > 50) despite all ventilator settings provided by the study protocol [28].

A dedicated polyfunctional feeding tube provided with an esophageal balloon (Nutrivent, Sidam, Mirandola (MO), Italy) to monitor esophageal pressure, estimate pleural pressure, and compute transpulmonary pressure will be placed in all enrolled patients after inclusion. The correct placement of the catheter and the adequate filling of the balloon will be confirmed by an occlusion test (airway pressure/esophageal pressure ratio will be recorded: 0.8–1.2 will be considered acceptable); the occlusion test will be repeated before any measurement is done to ensure the recordings of reliable values [29, 30].

A closed endotracheal suctioning system will be preferentially used in all the enrolled patients.

After the enrollment, mechanical ventilator will be set according to the following strategy: *V*_T_ = 6 mL/kg of predicted body weight; inspiratory flow set at 60 l/min resulting in an end-inspiratory pause of 0.3–0.5 s; respiratory rate 20–35 to maintain pH > 7.30, PEEP set so that the plateau (*P*_PLAT_) pressure will be within the following limits: *P*_PLAT_ = 28–30 cmH_2_O (EXPRESS PEEP), FiO_2_ set to achieve a SpO_2_ > 88–95% and not higher than 90%. In case of hypercapnia with pH < 7.30 despite a respiratory rate = 30–35, an increase in *V*_T_ up to 8 ml/kg will be allowed over the entire course of the study.

Predicted body weight (PBW) will be calculated according to the following formulas [3]:
$$ \mathrm{Males}:\mathrm{PBW}\ \left(\mathrm{kg}\right)=50+0.91\ \left(\mathrm{height}\ \mathrm{in}\ \mathrm{cm}-152.4\right) $$$$ \mathrm{Females}:\mathrm{PBW}\ \left(\mathrm{kg}\right)=45.5+0.91\ \left(\mathrm{height}\ \mathrm{in}\ \mathrm{cm}-152.4\right) $$

After 30 min with these settings to standardize lung volumes at maximum recruitment, a new ABG will be recorded. Afterwards, a 5-step decremental PEEP trial (EXPRESS PEEP to PEEP 5) will be conducted with the dedicated software on the ventilator (Inview PEEP, GE). Each step will last 8 min, and EELV will be measured with a 0.2 change in the FiO_2_. In case of evident airway closure [31, 32], the minimal PEEP tested in the PEEP trial will be the one providing a PEEP_TOT_ = airway opening pressure [32].

PEEP-induced lung recruitment across each PEEP step (Rec) will be computed as follows:
23$$ \mathrm{Rec}=\left({\mathrm{EELV}}_{\mathrm{PEEP}\mathrm{high}}-{\mathrm{EELV}}_{\mathrm{PEEP}\mathrm{low}}\right)-\left[\left({\mathrm{PEEP}}_{\mathrm{high}}-{\mathrm{PEEP}}_{\mathrm{low}}\right)\times {\mathrm{Compliance}}_{\mathrm{PEEP}\mathrm{low}}\right] $$

After the PEEP trial, a one-breath derecruitment maneuver from PEEP 5 to PEEP 0 will be conducted to assess baseline functional residual capacity (FRC) that will be measured as the difference between EELV at PEEP 5 and the lung volume increase above FRC, measured as the difference in expired tidal volume as PEEP is decreased from 5 to 0 cmH_2_O in one breath with respiratory rate ≤ 8 breaths per minute. In particular, the lung volume due to the presence of PEEP 5 (PEEP5_volume_) will be measured by subtracting the insufflated *V*_T_ from the expired *V*_T_ during a 5-s exhalation (respiratory rate < 8) just after PEEP is reduced from 5 to 0.
$$ \mathrm{FRC}={\mathrm{EELV}}_{\mathrm{PEEP}5}-\mathrm{PEEP}{5}_{\mathrm{volulme}} $$

This procedure will not be conducted in patients with airway closure.

In particular, when interpreting the results of the PEEP trial, Rec across two adjacent PEEP levels will be normalized to the changes in the effective PEEP (total PEEP) applied: REC_IND_/cmH_2_O will be computed as REC divided by the PEEP difference. For each PEEP range, the recruitment-to-inflation ratio (RI) will be then calculated as previously described [19, 33]:
$$ \mathrm{RI}={\mathrm{REC}}_{\mathrm{IND}}/{\mathrm{Compliance}}_{\mathrm{PEEPlow}}. $$

Each patient will be then randomized to undergo mechanical ventilation according to the two PEEP-setting protocols described in the next paragraph. Randomization will be stratified according to the volume of effective lung recruitment during the PEEP trial, as described in the “Randomization and record keeping” section.

Patients for whom the measurement of the EELV is not be feasible due to any technical reason will not be randomized and accurately recorded on the screening log.

